### Secondary End Points

Secondary end points include cost-effectiveness, health risk, and (self-reported) disease burden (refer to Table S1 in Multimedia Appendix 1). Cost-effectiveness will be evaluated through the ICER, which is the ratio of the difference in costs to incremental benefits between the online interactive lifestyle intervention program and general nutrition recommendations. For the cost-effectiveness analysis, we will calculate the quality-adjusted life years (QALYs) and total costs. QALYs express the impact of the disease on patients’ health over time. Living in perfect health corresponds to a QALY of 1 and a QALY of 0 reflects death [29]. QALYs are determined by calculating the area under the curve of the EQ-5D-5L [30]. Costs are divided into direct and indirect costs. We will analyze direct and indirect costs from a societal perspective. Direct costs are the costs of treatment and medical consumption, whereas indirect costs are costs due to loss of productivity [31]. Medication costs are calculated from doses reported in the patients’ case records, valued according to the Dutch National Health Care Institute [32]. Medical consumption, including duration of hospitalizations and admission diagnosis, are recorded every 3 months with the Institute for Medical Technology Assessment medical consumption questionnaire. We will use the Dutch average length of stay by diagnosis if the duration of hospitalization is unknown. Indirect costs include not fully functioning (presenteeism), sick leave (absenteeism), and reduction in work time [33]. Work Productivity and Activity Impairment (WPAI) outcomes are expressed as impairment percentages, with higher numbers indicating greater impairment and less productivity.

The health risk is assessed by measuring weight, BMI, and waist circumference. BMI is calculated by dividing the patient’s weight (kg) by the square of their height (m). A BMI ranging from 18.5 to <25 is classified as a healthy weight. A BMI between 25 and <30 is categorized as overweight, while a BMI ≥30 is considered obese. Conversely, a BMI <18.5 is classified as underweight [34]. Sex-specific thresholds for waist circumference are associated with an elevated risk of metabolic complications. In males, a waist circumference ≥94 cm is linked to an increased risk, whereas a measurement of ≥102 cm corresponds to a substantially increased risk. For females, these thresholds are ≥80 cm and ≥88 cm, respectively [34].

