Disease burden is measured through the following PRO measurements: GH, pain, morning stiffness, fatigue, functional ability, and quality of life. GH, fatigue, and pain are measured with a VAS (0‐100 mm), whereby higher scores reflect greater severity. The MCIDs for the aforementioned outcomes are ≥10 [35-37]. Fatigue is also measured with the Functional Assessment of Chronic Illness Therapy-Fatigue questionnaire (FACIT-F) [38]. The FACIT-F consists of 13-items with a 7-day recall period. Items are scored on a 0‐4 response scale with anchors ranging from “Not at all” to “Very much so.” All items are summed to create a single fatigue score with a range from 0 to 52 and higher scores represent less fatigue [38]. The MCID is 15.9 [39]. Morning stiffness (severity and duration in min) is measured with a Numeric Rating Scale and is interpreted similarly to GH. The MCID for morning stiffness is ≥1 [40]. Functional ability is measured with the Health Assessment Questionnaire [41]. Higher Health Assessment Questionnaire scores indicate poorer function, and the MCID is 0.22 [41,42].

Quality of life is measured with the EQ-5D-5L (MCID ≥0.04) [43,44]. Higher scores represent a higher quality of life. We will also use the 36-item Short-Form Health Survey (SF-36) that assesses 8 domains on a scale of 0‐100, with higher scores indicating a better health status [45]. The SF-36 addresses the following domains: physical functioning, bodily pain, role limitations due to physical health problems and social or emotional problems, mental health, vitality, and GH perceptions. These domains are also combined into a physical and mental component score. The MCIDs for the physical component score and mental component score are 2.5 and 5, respectively [30,45,46].

Although the primary outcome will be assessed after 12 months of follow-up, we will follow all participants for 2 years to determine the long-term effect of the lifestyle intervention and whether the intervention has led to a permanent behavioral change.

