#### Secondary End Points Analyses

The ICER will be used as an outcome for the cost-effectiveness analysis. The ICER is the ratio of the difference in total costs to incremental benefits (QALYs) between both management approaches. Total costs are divided into health care (direct) and productivity (indirect) costs, which will be analyzed from a societal perspective [31]. QALYs are calculated as the area under the curve of the EQ-5D-5L [30]. A probabilistic sensitivity analysis will be performed for the estimation of the ICER by bootstrapping with 1000 iterations using a Monte Carlo simulation. Results will be plotted in a cost-effectiveness plane, which will be used to estimate the 95% CI of the ICER. Additionally, a cost-acceptability curve will be extracted to show the probability of each intervention being cost-effective at different levels of willingness-to-pay thresholds in comparison with each other. Sensitivity analysis will be performed to assess the main drivers of cost-effectiveness.

Other secondary end points are health risk, weight, BMI and waist circumference, and PROs, including GH, pain, morning stiffness, fatigue, functional ability, and quality of life, at baseline, after 3 months, 6 months, 1 and 2 years of follow-up, and over time between both groups. A Student *t* test, chi-square test, or Wilcoxon rank-sum test will be used to compare the difference in aforementioned outcomes at fixed time points, when appropriate. Additionally, a mixed model with an unstructured covariance matrix will be used to compare outcomes over time. In all analyses, we will correct for our randomization minimization procedure. Moreover, the PRO difference will be weighed against the MCID.

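### The promised 95% CI for the ICER has no bounded, ordered form if the 95% interval for the QALY difference includes zero, and the plan sets no condition for that case

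*Protocol article*

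**What the plan says.** Under Secondary End Points the protocol states: "Cost-effectiveness will be evaluated through the ICER". Under Secondary End Points Analyses it defines the measure: "The ICER is the ratio of the difference in total costs to incremental benefits (QALYs) between both management approaches". The denominator comes from utilities ("QALYs are calculated as the area under the curve of the EQ-5D-5L"). The numerator is broad: "Total costs are divided into health care (direct) and productivity (indirect) costs, which will be analyzed from a societal perspective".

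Uncertainty is to come from "bootstrapping with 1000 iterations using a Monte Carlo simulation", and then: "Results will be plotted in a cost-effectiveness plane, which will be used to estimate the 95% CI of the ICER". The section does not say how the interval is read from the plane, and it attaches no condition about where the replicates fall. It also plans a further summary: "a cost-acceptability curve will be extracted to show the probability of each intervention being cost-effective at different levels of willingness-to-pay thresholds".

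The protocol gives no expected QALY difference, cost difference or SD for either. Under Sample Size, the trial is sized on remission or successful tapering.

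**The concern.** The ICER is a ratio whose denominator may be close to zero. When bootstrap QALY differences take both signs, two things fail.

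- **Continuity.** As the QALY difference passes through zero, the ratio jumps between plus and minus infinity.
- **Order.** A cost difference of +1000 with a QALY difference of +0.02 gives 50,000. So does −1000 with −0.02, which means the opposite: cheaper and worse instead of dearer and better. A negative ratio may mean cheaper and better or dearer and worse.

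Two limits taken from such a cloud do not run from favourable to unfavourable. Cost-effectiveness is the first secondary objective listed, and the Discussion says the authors hope the results will move policymakers and insurers towards reimbursement. Those readers are likely to look at the ICER and its interval.

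**Working it through.** **1. The protocol's own figure.** There is no figure for the ICER to reproduce. The sample size does reproduce: 30% versus 50%, two-sided alpha 0.05, power 80%, unpooled variance:

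n = (1.960 + 0.842)² × (0.30×0.70 + 0.50×0.50) / 0.20² = 90.3 per arm; 90.3 / 0.90 = 100.3.

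This agrees with the stated 100 per group including 10% dropout, so about 90 per arm are evaluable.

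**2. When a bounded interval exists.** The 95% (Fieller) set for the ICER is every λ satisfying (ΔC − λΔQ)² ≤ 1.96² × Var(ΔC − λΔQ). This is a quadratic in λ with leading coefficient ΔQ² − 1.96² × SE(ΔQ)². The set is a bounded interval only if that coefficient is positive, that is, if |ΔQ| / SE(ΔQ) > 1.96. This is the condition that the 95% interval for the QALY difference excludes zero. The cost difference does not enter it. Rays through the origin of the plane meet the same limit, because the wedge then takes in the vertical axis.

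**3. How often that condition fails.** SE(ΔQ) = SD × √(2/90) = 0.149 × SD. The SDs and gains are assumptions. The only anchor in the protocol is the EQ-5D-5L MCID of 0.04, read here as a gain held for one year. Worked case, gain 0.04 and SD 0.10: SE = 0.0149, z = 2.68, Φ(1.96 − 2.68) = 0.235, or 0.239 with the t distribution on 178 df. Chance that the 95% interval for ΔQ includes zero (t-based):

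| True QALY gain | SD 0.10 | SD 0.15 | SD 0.20 | SD 0.25 |
|---|---|---|---|---|
| 0.02 | 73% | 86% | 90% | 92% |
| 0.04 | 24% | 57% | 73% | 81% |
| 0.08 | 0% | 5.5% | 24% | 43% |

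With no true gain it is 95% throughout. Scaling both gain and SD to two years leaves z unchanged. Adjusting for baseline utility would lower the SD and move the result leftwards in the table.

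**4. What the cloud can look like.** Illustration with assumed inputs: ΔQ 0.02 (SE 0.025), ΔC 500 (SE 700), independent normal.

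- Quadrant shares: dearer and better 60%, cheaper and better 19%, dearer and worse 16%, cheaper and worse 5%.
- Point ICER: 500 / 0.02 = 25,000. The 2.5th and 97.5th percentiles of the ratio are about −307,000 and +337,000.
- Of the negative ratios, 16.1 / (16.1 + 18.7) = 46% are dearer and worse.
- Net monetary benefit at 50,000 per QALY: 50,000 × 0.02 − 500 = 500. SE = √(1250² + 700²) = 1433, so the 95% CI is −2,308 to 3,308. This interval is finite and ordered.

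**5. Cost crossing alone.** In simulations with a QALY gain of 0.16 (SD 0.20) and a cost difference of 0 or 500 (SD 8000), the cost interval included zero in 95% and 93% of trials. The percentile interval for the ICER still covered the true value in 94.9% and 95.3%, and Fieller's set was bounded in at least 99.9%. It simply ran from negative (dominant) to positive.

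**The case against.** The strongest reply has four parts.

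**The method of extraction is not stated.** A reader might infer that percentiles of the raw ratio will be used. The text does not say so; rays or an ellipse on the plane are equally consistent with it, and such detail may sit in a fuller document. This stands as far as it goes: the percentile limits in step 4 only illustrate one way of doing it. It does not remove the point, because the article itself commits to the interval without a condition, and step 2 holds for rays as well as for percentiles.

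**Likelihood is not shown by the documents.** A reader might infer that the problem is probable in this trial. The protocol gives no QALY effect or SD, so the table is conditional. At a gain of 0.08 with SD up to 0.15, or a gain of 0.04 with SD 0.10, the QALY interval would more often exclude zero.

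**Crossing zero on cost.** A reader might infer that replicates on both sides of a zero cost difference also invalidate the interval. Step 5 shows they do not. A rule allowing an ICER interval only when all replicates lie in one quadrant would therefore withhold valid intervals.

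**The harm is limited.** The plane shows the quadrants, and the acceptability curve is valid wherever the replicates fall. Nor does percentile coverage fail everywhere: with SD 0.20 and a cost difference of 1000 (SD 5000 or 10,000), it was 92% to 98% for gains of 0.01 to 0.08, dropping to zero only as the gain approached nothing. All this lowers the stakes. It does not make the limits ordered, and the promised interval would still be reported.

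**Conclusion.** The point holds in a bounded form. The protocol commits to a 95% CI of the ICER in all circumstances, yet no bounded, ordered interval exists when the 95% interval for the QALY difference includes zero. Whether that happens depends on quantities the protocol does not give. Under the assumed SDs of 0.10 to 0.25 and 90 per arm, it is common at gains up to the MCID and ranges from negligible to fairly frequent at twice the MCID. A gain well above the MCID cannot be presumed: patients enter in low disease activity, and the trial was not sized for QALYs. The primary analysis is unaffected, and the planned plane and acceptability curve remain sound.

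**What to change.** Replace the sentence on the 95% CI of the ICER with a commitment to report, from the same 1000 replicates:

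1. the QALY difference and the cost difference, each with its own 95% CI;
2. the share of replicates in each quadrant of the plane;
3. incremental net monetary benefit with a bootstrap 95% CI at willingness-to-pay values named in advance;
4. the acceptability curve already planned;
5. the ICER as a point estimate, with a 95% CI, by a stated method, only if the 95% interval for the QALY difference excludes zero.

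This changes analysis wording only and needs no new data or extra bootstrap. The cost is slightly more reporting and possibly a paper without an ICER interval. The protocol gives the last visit as May 2026, with analysis to follow. The change should be dated and made before costs and QALYs are compared by group.

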### Randomization and Blinding

Patients are randomized with a 1:1 allocation ratio into the intervention group (participating in the online, interactive lifestyle intervention program) or the control group (receiving general nutrition recommendations), using ALEA clinical software (ALEA Clinical B.V.). The allocation sequence was balanced for diagnosis (RA or PsA). Patients, treating physicians, RNs, and researchers will know to which group patients are randomized. The principal investigator will generate the allocation sequence and will assign participants to interventions using ALEA clinical software. RNs will enroll participants and do not have access to the randomization sequence. During statistical analysis, treatment allocation will remain concealed through the use of masked group labels.

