### Participant Timeline

Patients will be assessed at baseline and after 3, 6, 12, and 24 months. At each visit, patients will fill out online questionnaires (~30 min) and are assessed by the RN, who calculates the DAS28 or DAPSA depending on the diagnosis. Study visits will take 30 minutes or less. The timeline and extensive data collection overview are shown in Figure 2 and Table 2. Data collection is the same for both the intervention group and the control group.

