### Sample Size

The HELIA is a superiority trial, powered to detect a 20% difference in DAS28 and DAPSA remission and/or successful tapering of DMARD treatment after 12 months of follow-up. Meeting either criterion is sufficient to qualify for the primary outcome. Murray et al [55] showed that after the first year of diagnosis, remission rates are up to 30%. Although tapering of treatment is still not standard of care, previous research has shown that tapering of treatment in patients with LDA is possible [56]. Based on these data, we assumed that 30% of the patients in the control group, general nutrition recommendations, will reach remission or be able to successfully taper their medication and that this will be 20% higher in patients who will follow the online, interactive lifestyle intervention program. Thus, to detect this 20% difference using a significance level of *α*=.05 (2-sided) and a power of 80%, 100 patients per group (~75 RA and ~25 PsA) are needed, also taking a 10% dropout ratio into account, which is based on previous trials conducted in the Erasmus MC [57,58].

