#### Primary End Point Analyses

The primary end point is the proportional difference in DAS28 and DAPSA remission and/or those who were able to taper their medication without having a disease flare after 12 months of follow-up between patients with IA who followed the lifestyle intervention program and those who received general nutrition recommendations [23,26]. Meeting either criterion is sufficient to qualify for the primary outcome. Logistic regression will be used to compare aforementioned differences at 12 months, in which intervention allocation, diagnosis (RA or PsA), biologic or targeted synthetic DMARD usage at randomization (yes or no), age (years), and sex are the covariates. If baseline imbalances in CRP, tender and swollen joint counts between both interventions occur, we will also correct for these imbalances.

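### The tests named for secondary outcomes at fixed visits have no term for the correction promised for all analyses, and they leave the baseline values unused

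*Protocol article*

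**What the plan says.** Under Secondary End Points Analyses, the health-risk measures and patient-reported outcomes (PROs) are to be compared "at baseline, after 3 months, 6 months, 1 and 2 years of follow-up, and over time between both groups". The method for single visits is a Student t test, "chi-square test, or Wilcoxon rank-sum test will be used to compare the difference in aforementioned outcomes at fixed time points". For the longitudinal comparison, "a mixed model with an unstructured covariance matrix will be used to compare outcomes over time". The paragraph then adds "In all analyses, we will correct for our randomization minimization procedure" and says that PRO differences will be judged against the MCID.

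Three other places bear on this:

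- Randomization and Blinding: "The allocation sequence was balanced for diagnosis (RA or PsA"). No other balancing factor is named.
- Participant Timeline: "Patients will be assessed at baseline and after 3, 6, 12, and 24 months". Table 2 shows weight, BMI, waist circumference and most PROs at all five visits. The SF-36 is collected only at baseline, 12 and 24 months.
- Primary End Point Analyses: the primary comparison is a logistic regression whose covariates include diagnosis, alongside treatment arm, use of a biologic or targeted synthetic DMARD, age and sex. So the primary analysis does carry diagnosis.

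**The concern.** The paragraph names specific tests and then attaches a promise that those tests, in standard form, cannot keep. A two-sample t test, a chi-square test and a rank-sum test each compare two groups without covariates or strata. The mixed model can hold a diagnosis term; the fixed-visit tests as named cannot.

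The tests also ignore each patient's own starting value. Baseline appears in the paragraph only as one more time point at which the groups are compared. In a randomized trial that comparison tests the allocation, not a treatment effect.

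Comparisons at specific time points are part of the stated secondary objective on disease impact. With both an unadjusted test and a mixed model in the plan, the same outcome at the same visit can have two different estimated differences. The article does not say which one is set against the MCID.

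**Working it through.** **1. The article's own figure.** The only sample-size figure is for the primary end point, and this point does not dispute it. Inputs from Sample Size: 30% against 50%, two-sided alpha 0.05, 80% power, 10% dropout. With unpooled variance, n = (1.960 + 0.842)² × (0.21 + 0.25) / 0.20² = 91 per group, and 91/0.9 = 102. With pooled variance it is 93, and 93 × 1.1 = 103. The stated 100 per group is reproduced to within 3%. No secondary outcome has a power statement, so the power figures below are illustrations.

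**2. Gain from using baseline.** The article gives neither a correlation r between baseline and follow-up nor an SD, so r is assumed. With equal SDs at both visits, the variance of the between-group difference relative to raw follow-up values is:

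- raw follow-up: 1
- change from baseline: 2(1 − r)
- baseline-adjusted: 1 − r²

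Adjusted against change scores, the ratio is (1 − r²) / [2(1 − r)] = (1 + r)/2. If the unadjusted comparison has 80% power, power after adjustment is Φ(2.802/√ratio − 1.960).

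| Assumed r | Ratio vs raw | Variance cut | Power | Ratio vs change | Variance cut | Power |
|---|---|---|---|---|---|---|
| 0.5 | 0.75 | 25% | 89.9% | 0.75 | 25% | 89.9% |
| 0.6 | 0.64 | 36% | 93.8% | 0.80 | 20% | 87.9% |
| 0.7 | 0.51 | 49% | 97.5% | 0.85 | 15% | 86.0% |

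In terms of detectable difference with 90 completers per group (100 × 0.9), the t test on raw values has 80% power for 2.802 × √(2/90) = 0.418 SD. Baseline adjustment lowers this to 0.418 × √(1 − r²):

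| Assumed r | Detectable difference | Power for a 0.3 SD difference |
|---|---|---|
| no adjustment | 0.418 SD | 52% |
| 0.3 | 0.398 SD | 56% |
| 0.5 | 0.362 SD | 64% |
| 0.7 | 0.298 SD | 81% |

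A change score is no safe substitute. At r = 0.3 its detectable difference is 0.418 × √1.4 = 0.494 SD, worse than the raw t test.

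**3. Effect of leaving diagnosis out.** Sample Size gives about 75 RA and 25 PsA per group. If diagnosis shifts the outcome by g within-diagnosis SDs, the t test counts an extra 0.75 × 0.25 × g² = 0.1875g² as noise, although balancing has removed it from the comparison. A simulation of 20,000 trials with 100 per group, exactly balanced on diagnosis, gave these type I error rates (simulation standard error about 0.15 percentage points):

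| Shift g | t test | With diagnosis term |
|---|---|---|
| 0 | 5.2% | 5.2% |
| 0.25 | 4.6% | 4.7% |
| 0.5 | 4.3% | 4.7% |
| 1.0 | 3.3% | 5.2% |

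So omitting diagnosis makes the test conservative, and clearly so only when diagnosis is a strong predictor. It does not inflate false positives.

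**The case against.** The strongest reply is that this is loose wording in a condensed article. The correction sentence directly follows the mixed-model sentence, and that model can carry the term. Stratified or regression versions of the named tests exist (Cochran-Mantel-Haenszel, van Elteren, linear regression), and a statistical analysis plan could specify them. It follows that a reader who infers that the comparisons cannot be run goes too far: the tests run, and only the promised correction has no place in them as named. What remains is that the article does name the tests and does say all analyses.

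A second reply is that the compared difference could mean change from baseline. Listing baseline among the compared time points fits raw values better, but the wording does not settle it. On the change-score reading the gain is smaller and shrinks as the correlation rises. Diagnosis is still uncorrected.

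A third reply is that the mixed model already uses baseline. It may, but the article does not say how baseline enters. If baseline is simply another response with its own free group difference, complete data give back the raw visit difference. The precision is recovered when baseline is a covariate or the groups share one baseline mean.

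A reader might also infer that the balancing factors are stated inconsistently, because one section describes a balanced allocation sequence and another speaks of minimization. The text does not support that. Only diagnosis is named, nothing conflicts with it, and minimization is one way to balance. At most the label for the method is unclear. Nor is the pooling of rank-sum or chi-square results over 40 imputations an error here: methods exist, and the choice can be left to the analysis plan.

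**Conclusion.** The point holds as one of precision and coherence in the fixed-visit secondary comparisons. The promised correction has no place in the tests as named, baseline information goes unused, and two visit-level estimates could compete when set against the MCID.

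The size rests on an assumed correlation of 0.5 to 0.7. Variance falls by 25% to 49% against raw values, or by 25% down to 15% against change scores. For a comparison that would otherwise have 80% power, that means about 90% to 97%, or about 90% down to 86%.

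A reader might infer that the secondary results would be invalid or the primary result compromised. Neither follows. Type I error is at most slightly conservative, and only if diagnosis predicts the outcome. The primary logistic regression already includes diagnosis. A mixed model that uses baseline properly is also unaffected. This is worth changing, but it is not critical.

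**What to change.** For health-risk outcomes and PROs, replace the fixed-time tests with visit-specific contrasts and 95% CIs from the planned unstructured mixed model. Its terms would be arm by visit, diagnosis, and baseline, entered either as a covariate or through a common baseline mean for both arms. Report contrasts only at visits where the outcome is collected: 3, 6, 12 and 24 months for most, and 12 and 24 months for the SF-36. State that these contrasts are the differences weighed against the MCID. Use logistic models with diagnosis for any binary outcome. Drop the between-group test at baseline.

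The cost is small but not nil. The Results section says that analysis plans have not changed since registration, so this must be recorded as a dated change before analysis begins; analysis is due to follow the last visit in May 2026. Without the rank-sum test, the plan also needs a stated approach for skewed outcomes. No new data are required.
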